### 2.5. Sample Size Calculation

To determine the appropriate sample size for this study, a power analysis was conducted using G*Power 3.1 software [43]. The analysis was based on a repeated-measures design with two groups (experimental vs. control) measured at baseline and post-intervention. The following parameters were used: Effect Size (Partial η^2^) = 0.06 (medium effect); Cohen’s d = 0.50. Alpha Level (α) = 0.05 (5% significance threshold); power (1 − β) = 0.80 (80% probability of detecting a real effect); two measurement points (pre- and post-intervention); and two groups (experimental and control). According to the established criteria, the minimum requisite sample size for achieving adequate statistical power was computed to be 34 participants, with 17 participants allocated to each group. The objective of this study is to include and evaluate 40 participants, with 20 subjects in each group, to account for potential participant dropout. This methodological approach ensures that the study can detect meaningful differences in vertical ball strength, muscle activation (EMG), dynamic balance, angular velocity, muscle hypertrophy, and psychological impact (SWLS scores) with sufficient precision.

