### 3.5. Statistical Analysis

All statistical analyses will be conducted using IBM SPSS Statistics (version 29, IBM Corp., Armonk, NY, USA). Normality checks will be performed via the Shapiro–Wilk test (small to medium samples) supplemented by histograms, Q-Q plots, and skewness/kurtosis assessments.

Reliability Analysis:SWLS questionnaire consistency will be assessed using Cronbach’s alpha (>0.70).Item-total correlations will ensure meaningful contributions to overall scoring.

Inferential Testing:Within-group comparisons: paired samples *t*-test (normal data) or Wilcoxon Signed-Rank test (non-parametric).Between-group comparisons: independent samples *t*-test (parametric) or Mann–Whitney U test (non-parametric).Repeated-measures ANOVA will assess pre- and post-intervention changes, applying Bonferroni corrections for multiple comparisons.

Effect Size and Correlations:Cohen’s d for *t*-tests, Partial Eta Squared (η^2^) for ANOVA.Pearson’s correlation (parametric) or Spearman’s rank correlation (non-parametric) to explore variable associations.

Additional Measures:Homogeneity of variance was tested via Levene’s test.Intention-to-treat (ITT) analysis for participant dropout management, using multiple imputation techniques to mitigate bias.

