## 5. Study Limitations

There are potential limitations that should be acknowledged to strengthen transparency and validity. Here are some key limitations to consider:Sample Size Constraints: Despite the power analysis confirming the minimum sample size of 34 participants, this relatively small cohort may limit the detection of subtle training effects, reducing generalizability to larger, diverse populations.While the inclusion of healthy adults aged 25–35 provides a physiologically stable cohort for detecting training-specific adaptations, it also limits the generalizability of findings to other age groups. This age bracket was deliberately chosen to mitigate the impact of maturation-related neuromuscular developments, which could otherwise compromise the interpretation of results. Subsequent studies should endeavor to extend the age range in order to investigate the protocol’s influence across a more extensive range of demographics, including older adults and sedentary populations.Intervention Duration: An eight-week timeframe may be sufficient to capture short-term neuromuscular and biomechanical adaptations, but it may not fully reflect long-term hypertrophic changes, particularly in deep-core muscle developmentParticipant Adherence and Training Variability: Differences in individual recovery rates, motivation, and external physical activity levels may introduce inconsistencies in training adherence, affecting final outcome measures.Measurement Variability: While EMG, force plate, ultrasound imaging, and motion tracking provide objective data, inherent technical limitations (such as electrode placement sensitivity, force plate calibration, and operator precision in ultrasound scans) may introduce minor variability in recorded results.Control Group Considerations: Participants in the control group will not undergo structured core training, but external exercise habits beyond the study’s scope may influence baseline and post-intervention assessments, creating additional variability.Lack of Long-Term Follow-Up: While pre- and post-intervention assessments provide insights into immediate improvements, the absence of extended post-study evaluations limits our ability to determine the retention of training adaptations over months or years.It is acknowledged that the absence of pilot data constitutes a significant limitation. The designated laboratory was already reserved for other scheduled research activities prior to the commencement of the trial period, which precluded the execution of a pilot phase. A comprehensive preparatory pilot study would have necessitated an estimated four months of recruitment, analysis, and evaluation time.

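### The 34 participants give 80% power for a between-group difference in change of about 1.0 SD, not for the stated d = 0.50, where power is about 29%

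*Protocol article*

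**What the plan says.** Section 2.5 of the protocol article says that "a power analysis was conducted using G*Power 3.1 software". On the design it states: "The analysis was based on a repeated-measures design with two groups (experimental vs. control) measured at baseline and post-intervention". The inputs are "Effect Size (Partial η^2^) = 0.06 (medium effect", also given as Cohen's d = 0.50; "Alpha Level (α) = 0.05 (5% significance threshold"; and "power (1 − β) = 0.80 (80% probability of detecting a real effect". There are two groups and two measurement points. The conclusion is that "the minimum requisite sample size for achieving adequate statistical power was computed to be 34 participants, with 17 participants allocated to each group". The target is then raised to 40 (20 per group) to allow for dropout, and the section says this is enough to detect meaningful differences across six outcome domains.

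The section does not state the pre-post correlation, which ANOVA effect was powered, or which SD d refers to. Section 5 repeats the result: "Despite the power analysis confirming the minimum sample size of 34 participants". Section 3.5 plans between-group tests, a repeated-measures ANOVA with Bonferroni correction, and "Partial Eta Squared" as the ANOVA effect size.

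**The concern.** A two-arm comparison with 17 per group does not normally have 80% power for a standardised difference of 0.50, so 34 is suspiciously small. Cohen's f for a 2 × 2 interaction is easily mistaken for half of a two-group d. If that happened here, the trial is powered for an effect twice as large as the one it names.

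The stake is how the results are read. A reader who trusts Section 2.5 would take a null group comparison as evidence against a medium effect, when the trial would more often miss such an effect than find it. The caveat in Section 5 covers only subtle effects and reaffirms the 34.

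**Working it through.** **Inputs.** From Section 2.5: partial eta-squared 0.06, d = 0.50, alpha 0.05, power 0.80, two groups, m = 2 measurements, N = 34 (minimum) and 40 (planned). The pre-post correlation ρ is not stated; it is an assumption below, and a range is shown.

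**Step 1: reproduce 34.** Partial eta-squared 0.06 converts to f = √(0.06/0.94) = 0.2526, and d = 0.50 to f = d/2 = 0.25. For the repeated-measures interaction,

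λ = f² · N · m / (1 − ρ), with 1 and N − 2 degrees of freedom.

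With f = 0.25, ρ = 0.5 and N = 34, λ = 0.0625 × 34 × 2 / 0.5 = 8.5. On F(1, 32) this gives power 0.807. N = 32 gives 0.781, so 34 is the smallest even total. With f = 0.2526, power at 34 is 0.815. Other correlations do not return 34: with f = 0.25, ρ = 0.3 gives 46, ρ = 0.7 gives 22 and ρ = 0.8 gives 16. The between-group main effect at ρ = 0.5 would need 96 to 98.

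**Step 2: what effect is that?** In a 2 × 2 interaction with one SD throughout, f = 0.25 means that each cell deviates by ±0.25 SD. The group difference in pre-to-post change is then 4 × 0.25 = 1.0 SD. At ρ = 0.5 the SD of change is √(2(1 − 0.5)) = 1 raw SD, so this is also 1.0 SD of change.

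Check with a two-sample t-test on change, 17 per group, d = 1.0: noncentrality 1.0 × √(17/2) = 2.915, and 2.915² = 8.5. The power is the same, 0.807.

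On the ANOVA's own error term, λ = 8.5 corresponds to a partial eta-squared of 8.5/(8.5 + 32) = 0.21 (0.20 if N replaces the error degrees of freedom), not 0.06.

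**Step 3: power at the stated effect.**

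- *d = 0.50 scaled by the SD of change (or raw SD at ρ = 0.5), two-sided 0.05:* 29.3% with 17 per group and 33.8% with 20. Power of 80% needs 64 per group, 128 in total. A one-sided test with 17 per group would give only 41%.
- *Partial eta-squared 0.06 on the ANOVA's own error term:* 28–30% with N = 34, and 126–128 participants for 80%. This does not depend on ρ.
- *Smallest difference in change detectable with 80% power:* 0.99 SD of change with 34 and 0.91 SD with 40.

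**Step 4: sensitivity to the correlation.** If d = 0.50 is in raw SD units, the difference in SDs of change is 0.50/√(2(1 − ρ)):

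| ρ | Difference in SDs of change | Power, N = 34 | Power, N = 40 | Total N for 80% |
|---|---|---|---|---|
| 0.3 | 0.42 | 22% | 26% | 178 |
| 0.5 | 0.50 | 29% | 34% | 128 |
| 0.7 | 0.65 | 45% | 51% | 78 |
| 0.8 | 0.79 | 61% | 68% | 54 |
| 0.85 | 0.91 | 73% | 80% | 40 |

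With 34 participants, 80% is reached only at ρ of about 0.87.

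**The case against.** The strongest reply is that 34 is not a miscalculation and may belong to another contrast. The within-factor (time) test has the same λ of 8.5 and the same power, and there f = 0.25 is a pre-post change of 0.50 SD, so d = 0.50, partial eta-squared 0.06 and N = 34 all agree. A one-group paired t-test at a standardised change of 0.50 also gives 34 (power 80.8%). The hypotheses in Section 1.3 are worded as improvements under the programme, which fits this reading.

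It is true that 34 follows from inputs close to those stated, and that the powered effect is unnamed. But this reading does not support the power claim. The time effect averages over both arms, and Section 3.4.4 designs the control routine so that it produces no measurable change in hypertrophy, balance or dynamic power. An average change of 0.50 SD with no change among controls means 1.0 SD in the trained arm, the same doubled effect. Section 4.6 expects differences between the groups, so a randomised two-arm trial has to be powered for that contrast.

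A second reply is that the 29% and the 128 depend on an unstated correlation. For d in raw SD units that is right, and the table shows the range. A correlation high enough to rescue 80% power (about 0.87 with 34, about 0.85 with 40) would not have produced 34 in the first place. The partial eta-squared result does not depend on the correlation, although it does depend on reading 0.06 on the ANOVA's own error term rather than on the scale that reproduces 34.

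A third reply is that 40, not 34, is the target. At 40 and ρ = 0.5, power is still only 34%. Baseline-adjusted analysis (ANCOVA), which Section 3.5 does not list, would give about 37% with 34 and 43% with 40 at that correlation.

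**Conclusion.** The concern holds. The sample gives 80% power for a between-group difference in change of about 1.0 SD, not for the stated 0.50 SD: the effect is understated by a factor of two and the required total by nearly four (128/34 = 3.8). Power at a 0.50 SD difference is 29% with 34 and 34% with 40. This assumes a two-sided 0.05 test on change or the equivalent interaction test, and either ρ = 0.5 or d scaled by the SD of change. With d in raw SD units and ρ between 0.3 and 0.8, power is 22% to 61% with 34 and 26% to 68% with 40, below 80% throughout. Any Bonferroni correction across outcomes lowers these figures further. The fault lies in the effect attached to the number, not in how the number was computed.

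**What to change.** Keep the 40 participants and restate what they can detect. First confirm from the G*Power record which effect and which correlation were entered. If these were the interaction and 0.5, Section 2.5 could read:

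> With 34 evaluable participants (40 randomised), the trial has 80% power at two-sided alpha 0.05 to detect a between-group difference in pre-to-post change of about 1.0 SD (0.91 SD if all 40 are evaluable). This corresponds to a partial eta-squared of about 0.2 for the group-by-time interaction, assuming a pre-post correlation of 0.5. Under the same assumption, power for a difference of 0.50 SD is 29% with 34 and 34% with 40.

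Remove the medium-effect label and d = 0.50 as the effect for which the trial has 80% power. Amend the sample-size sentence in Section 5 so that it says a medium effect would more likely be missed than found, rather than only subtle ones. If the record shows a different correlation or contrast, state that and recompute the between-group figures.

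The cost is wording only: no change to recruitment, measurements or conduct. The price is a less favourable detectable effect. Retaining the claim of 80% power at d = 0.50 would instead need about 128 evaluable participants at a correlation of 0.5.

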### 2.6. Description of the Study Instruments

This study employs a range of validated measurement instruments to accurately assess the effects of the eight-week core training intervention on muscle activation, hypertrophy, balance, and force application. To quantify the vertical impact force generated during the overhead medicine ball slam, a 3D dynamometer (Kistler, Winterthur, Switzerland) integrated with MARS performance analysis software will be used. This dynamometer will also be utilized to measure static balance parameters, ensuring a comprehensive analysis of lower limb stability under controlled conditions. EMG assessments will be conducted using a Biopac Systems Inc. machine (Goleta, CA, USA) with shielded surface electrode lead assemblies (model SS2, Biopac Systems Inc., Goleta, CA, USA) to record neuromuscular activity in the rectus abdominis (RA), external oblique abdominis (EO), and iliocostalis lumborum (IL) during exercise execution. EMG signals will be collected at a sampling rate of 1024 Hz using an amplifier/transmitter model TEL100 M (Biopak Systems Inc., Goleta, CA, USA), which exhibits a common mode rejection ratio exceeding 110 dB at 50/60 Hz, a bandwidth of 10–500 Hz, and an amplification gain of 1000. Data acquisition and processing will be performed using Acknowledge software (version 3.9.1, Biopac Systems) to ensure signal clarity and standardization across trials. Ultrasonography will be employed to measure deep core muscle thickness, particularly the transversus abdominis (TrA), internal oblique (IO), and lumbar multifidus (LM) at rest. These assessments will be performed using a computerized Aloka ProSound SSD 3500 SV ultrasound system (Aloka Co., Ltd., Tokyo, Japan) with a 6 cm transducer head operating at 13 MHz, ensuring high-resolution imaging of core musculature. Biomechanical analysis of torso and arm angular velocity during the medicine ball overhead slam will be conducted using Kinovea version 0.9.5 software (https://www.kinovea.org/download.html, accessed on 8 May 2025). This system will track angular momentum changes throughout the movement cycle, determining the final velocity of the ball at impact. High-definition motion capture will be facilitated using a PTZOptics Move 4K 20X NDI camera (PTZOptics, Downingtown, PA, USA) to ensure precision in kinematic assessments.

Anthropometric data, including height and body weight, will be recorded using an electronic balance with an integrated Seca stadiometer (Seca 220e, Hamburg, Germany). To evaluate the psychological impact of the intervention, participants will complete the Satisfaction with Life Scale (SWLS) questionnaire [44], providing insights into changes in subjective well-being throughout the study. The medicine balls used for overhead slam testing will be Energetics slam balls [(manufactured in Herzogenaurach, Germany, by Energetics (INTERSPORT Group))], ensuring consistent rebound and weight distribution across trials.

## 3. Procedure

### 3.1. Study Measuring Procedure

Both the experimental and control groups will undergo baseline and post-intervention measurements, scheduled at the neuromechanics laboratory of the Department of Physical Education and Sport Science, Aristotle University of Thessaloniki, in Serres. Testing sessions will be conducted by appointment, ensuring controlled environmental conditions across assessments. Upon arrival, participants’ anthropometric data—including weight, height, and age—will be recorded, alongside verification of personal contact details.

To optimize movement proficiency, participants will complete a brief warm-up routine in a designated laboratory space, ensuring sufficient joint mobility and neuromuscular readiness for the overhead medicine ball slam exercise. Following the warm-up, expert laboratory personnel will guide each subject through the measurement protocol, with a total session duration estimated between 30 and 40 min per participant.

The primary assessment will involve medicine ball overhead slam execution, during which force output will be recorded using a 3D dynamometer (Kistler, Winterthur, Switzerland) integrated with MARS performance analysis software. Simultaneously, EMG recordings will monitor muscle activation in the RA, EO, and IL, captured via bipolar surface electrodes (Biopac Systems Inc., Goleta, CA, USA). A high-definition PTZOptics Move 4K camera will document the angular velocity of the shoulder, hip, and knee joints from a standardized right-side view. To assess postural stability, participants will undergo a static balance evaluation, conducted using the Kistler 3D dynamometer while standing with eyes open. Additionally, deep-core muscle hypertrophy assessments will be performed via ultrasound imaging (Aloka ProSound SSD 3500 SV, Tokyo, Japan), measuring the TrA, IO, and LM at rest.

Psychological well-being will be evaluated using the Satisfaction with Life Scale (SWLS) questionnaire [45] to determine potential changes in the subjective quality of life resulting from the intervention.

### 3.2. Medicine Ball Overhead Slam Execution Protocol

Participants will follow precise movement instructions for Medicine Ball Overhead Slam to ensure consistency in execution.

CRITICAL STEPS:Neutral Spine Alignment-Ensure the lumbar and thoracic spine remain neutral throughout the movement to prevent hyperextension or excessive flexion.-Engage the TrA and deep-core stabilizers prior to initiating the slam.Controlled Upward Phase-Maintain a stacked ribcage position to prevent thoracic flare, ensuring optimal core bracing.-Avoid compensatory backward lean, ensuring spinal neutrality throughout the lift.Explosive Downward Phase with Proper Bracing-Initiate forceful exhalation (bracing technique) before slamming the ball to stabilize intra-abdominal pressure and minimize lumbar compression.-Keep elbows slightly bent upon ball impact to dissipate kinetic force efficiently, protecting shoulder joints from excessive stress.Ground Stability and Foot Positioning-Distribute weight evenly across the midfoot and heels to prevent forward displacement of force.-Maintain knee tracking aligned with toes, avoiding valgus collapse for joint integrity.Follow-Through Mechanics-Ensure post-impact recovery is smooth, preventing uncontrolled movement deviations that may compromise kinetic efficiency.-Allow arms to fully extend post-slam, avoiding abrupt tension in the upper trapezius and neck stabilizers.

### 3.3. Validation and Muscle Activation in the Medicine Ball Overhead Slam

The overhead medicine ball slam is a validated measure of explosive upper-body power, core strength, and neuromuscular efficiency, making it a reliable test for our study parameters. Research has shown its strong correlation with upper-limb power output in swimmers [46], enhanced throwing velocity and precision in handball players [47], enhanced performance in rotational power sports [48], and increased explosive strength through ballistic training [49]. The Schultz Slam Test (SST) further supports its validity as a core power assessment in football [50], while studies in cricket [51] and golf [52] confirm its test-retest reliability for evaluating rotational power and movement efficiency. These findings collectively justify its use as a standardized performance metric in our study. The overhead medicine ball slam primarily activates core musculature, serving as the central force generator while stabilizing the lower body for efficient energy transfer through the upper limbs.

The RA, obliques, and TrA collectively facilitate spinal flexion, rotational control, and deep-core stabilization, ensuring efficient force transmission during the downward slam. The deltoids, triceps, and latissimus dorsi play a significant role in the overhead phase, contributing to arm extension and controlled force application. Lower-body stabilization relies on the quadriceps and gluteus maximus, which assist in squat positioning and upward propulsion, reinforcing postural control throughout the movement cycle. Additional secondary muscle groups contribute to balance and coordination, including the calves (gastrocnemius and soleus), rhomboids, and erector spinae. These muscles facilitate ankle stability, scapular positioning, and spinal alignment, preventing excessive compensatory movement and ensuring efficient kinetic chain integration.

This exercise relies on muscle synergy, where the core initiates power generation, directing force through the upper limbs, while the lower body establishes a stable base for execution. By optimizing intermuscular coordination, the medicine ball overhead slam enhances functional movement patterns, improving athletic explosiveness, postural integrity, and neuromuscular responsiveness.

### 3.4. Study Intervention Protocol

This core exercise protocol has been developed for implementation in health clubs or for recreational fitness practitioners who require a core workout to prevent back pain or to enhance their core strength. Detailed instructions for the exercises of the entire protocol (warm-up, main core training, and cool down) can be found in Supplementary File S1.

Important notice: The exercises can be varied or replaced by corresponding exercises depending on the level and needs of each person. It is important to maintain the sequence of exercises and the designated rest and activity time periods outlined in the protocol.

#### 3.4.1. Warm-Up Protocol for Core Training (Approx. 6 min)

The exercises selected for the warm-up phase were designed to prepare the muscular and central nervous systems to manage the specific loads demanded by the core training protocol. The exercises that comprise the warm-up are enumerated in Table 1.

#### 3.4.2. Main Core Training Protocol (Approx. 30–32 min)

The structured eight-week core training program (Table 2) follows an optimized sequence designed to activate, strengthen, and enhance dynamic movement efficiency, ensuring neuromuscular coordination and injury prevention. The protocol consists of eight exercise triads, each incorporating core stability, core strength, and high-intensity core power exercises, performed for 45 s per exercise (2.15 min per exercise triad), with progressively increasing rest periods between triads. The interval between the initial and secondary triad of exercises is one minute. The interval between the secondary and third triad of exercises is one minute and ten seconds, and it gradually increases to two minutes by the conclusion of the seventh triad of exercises (see Table 2). The progression of training within this protocol allows for individual adaptation based on the practitioner’s experience level. Novice practitioners may perform fewer triads or extend recovery periods to ensure proper neuromuscular adaptation and prevent excessive fatigue. This approach allows for a gradual increase in workload while maintaining movement integrity and control. In contrast, advanced practitioners can modify the protocol by increasing the total number of triads, reducing rest intervals, or integrating additional explosive movement variations to enhance power development and neuromuscular efficiency. Regardless of experience level, breathing techniques remain a crucial component of execution, with a focus on bracing and controlled exhalation. Proper breath control optimizes force transfer, reinforces spinal integrity, and minimizes compensatory movements, ensuring both safety and effectiveness throughout the training process.

The structured progression of core training follows established principles to optimize neuromuscular adaptation. Beginning with core stability exercises, deep core muscles are activated to improve postural control and spinal alignment. Research has shown that stabilizing musculature plays a crucial role in force transmission and movement efficiency, emphasizing the importance of initiating training with stability-focused movements [2]. This phase prepares the kinetic chain for increased mechanical demand, reducing compensatory movements. These movements are executed at a controlled aerobic pace, emphasizing bracing and deep core engagement rather than rapid force production.

Following stability work, core strength exercises enhance force production and neuromuscular coordination, benefiting from pre-activated stabilizers. Strength training contributes to movement efficiency and biomechanical stability, supporting the transition from foundational activation to controlled force output [4]. This progression allows for improved kinetic chain integration, reinforcing motor control. These exercises follow a standard tempo, incorporating core bracing techniques, lateral breathing mechanics, and controlled execution to maximize muscle recruitment and stability.

The final phase of the sequence consists of high-intensity core power exercises, designed to maximize explosive force output and agility. Research on force–velocity relationships confirms that progressive sequencing from stability to strength to power enhances neuromuscular efficiency and reactive performance [3]. By concluding with high-intensity movement, the protocol ensures optimized power application, reinforcing dynamic stability and responsiveness. These exercises are performed above the anaerobic threshold, utilizing fast-paced movements with high muscular recruitment to promote optimal neuromuscular adaptation.

The selection of 45 s per exercise is based on scientific evidence supporting short-duration high-intensity training, which optimizes neuromuscular activation, endurance, and power development. Studies indicate that exercise bouts lasting between 30 and 60 s enhance muscle engagement and metabolic efficiency, making this duration ideal for core stability, strength, and power exercises [53]. Additionally, the total triad duration of 2 min and 15 s balances intensity and recovery, ensuring optimal neuromuscular engagement while preventing excessive fatigue, aligning with structured progression principles [54].

